### Economic analyses

#### Estimation of costs

The costs will be estimated from both a NHS and a patient participant perspective. The NHS costs include the cost of the treatments provided by NHS dentists and primary care and secondary use related to dental issues. The participant incurred costs include time and travel costs for making return visits to the dentist and payments for care received.

The quantity, unit cost and average cost per participant will be reported. Regression analysis will be used to report differences in costs between randomised groups, adjusting for baseline participant characteristics (e.g. minimisation variables). Bootstrapping is used to obtain confidence intervals surrounding the average cost estimates.

#### Estimation of benefits

Two different approaches are used to estimate the benefits of recall strategies: Willingness-to-Pay and QALYs. The recall strategies may vary in terms of health related outcomes (e.g. caries) as well as non-health outcomes, such as level of reassurance. The benefits of the recall strategies are therefore valued in monetary terms - willingness to pay (WTP) value. A DCE will be used to provide a framework to weight different process and outcomes measures. Discrete Choice Experiments are increasingly used in the evaluation of health care interventions to produce overall benefit scores for treatments as well as examine the absolute and relative importance of different outcomes considered as important. This approach has been adopted as measures such as quality adjusted life years typically used in economic evaluations may not be sufficient to capture the strength of preferences for differences in the process and outcomes of care associated with each intervention. A DCE is used to estimate the WTP values for the different recall strategies. The DCE presents individuals with a series of choices between different scenarios which vary in terms of frequency of routine check-ups, experience of oral health problems, and cost. The DCE will be administered to a nationally representative sample of the UK general population.

The sample size required for the DCE reflects the need for the sample to be larger than the number of independent variables and provide an adequate sample for each pre-determined subgroup e.g. dental attendance (regular, non-regular), non-smoker or current smoker; socio-economic status (high, medium, low), (12 subgroups in total and 30–100 per subgroup). Allowing for individuals to be present in a number of groups, the questionnaire will be sent to 1000 individuals ([12 × 50]x[100/60]). Appropriately specified logistic regression analysis is used to model the preference as a function of the attributes. Marginal rates of substitution between the coefficients of the attributes and costs represent WTP.

Quality of Life is measured using the generic EQ-5D-3 L instrument. EQ-5D-3 L is a standardised instrument for use as a measure of health outcome. The EQ-5D-3 L scores are measured at baseline, and annually as part of the patient questionnaire. Quality Adjusted Life Years are estimated by estimating the area under the lines that link the utility scores obtained at the different time points. In case of any baseline differences in the EQ-5D-3 L scores, regression analysis is used where patient specific QALYs are modelled as a function of the baseline EQ-5D-3 L score and arm of the trial. The coefficient of arm of the trial represents the QALY differences adjusted for baseline differences.

#### Estimation of cost-effectiveness

The economic analysis will assess whether fixed-period 24-month or risk-variable-adjusted length dental recall represents an efficient use of NHS resources compared to the traditional fixed-period six-month recall. Cost-effectiveness will be measured in terms of the incremental cost per QALY gained and in terms of net benefits (cost-utility analysis and cost-benefit analysis).

The incremental cost per QALY is estimated by dividing the difference in mean total costs by the difference in QALYs between the arms of the Trial. This ratio can be compared to the conventional threshold of £30,000 per QALY. Bootstrapping is used to generate Cost-Effectiveness Acceptability Curves (CEAC). The CEAC shows the probability that the different recall strategies are cost-effective compared to usual care at various thresholds of cost-effectiveness. The threshold represents the decision-maker’s willingness to pay for an additional QALY. The CEAC represents the joint uncertainty surrounding the cost and QALY pairs.

The WTP values are mapped to recall strategy and trial outcomes and are directly compared with the costs to produce net benefits for each recall strategy. The recall strategy with the highest incremental net benefit compared to six-monthly recall is the most efficient option. A net benefit curve is produced which shows the probability of the net benefits being larger than different potential thresholds.

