**Methods:**

This is a four year multi-centre, parallel-group, randomised controlled trial with blinded outcome assessment based in dental primary care in the UK. Practitioners will recruit 2372 dentate adult patients. Patient participants will be randomised to one of three groups: fixed-period six month recall, risk-based recall, or fixed-period twenty-four month recall. Outcome data will be assessed through clinical examination, patient questionnaires and NHS databases. The primary outcomes measure gingival inflammation/bleeding on probing and oral health-related quality of life.

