**Discussion:**

INTERVAL will provide evidence for the most clinically-effective and cost-beneficial recall interval for maintaining optimum oral health in dentate adults attending general dental practice.

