### Objectives

The primary objectives are to compare (1) gingival inflammation and (2) oral health-related quality of life (OHRQoL) of dentate adults receiving a dental check-up at different recall intervals over a four year period:Fixed-period six month recallRisk-based recallFixed-period 24 m recall

The secondary objectives are to compare the effect of the three recall strategies on periodontal probing depths, dental caries, calculus, preventive and interventive dental treatment, patient anxiety, patient satisfaction with care, oral health knowledge, attitudes and behaviours. The cost-effectiveness and cost-benefit of the three recall strategies will also be assessed as part of the economic evaluation.

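### In the stratum with three options, the acceptability curves are defined pairwise against six-month recall and do not show how certain the choice of the best strategy is

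*Protocol article*

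**What the plan says.** All statements are in the Protocol article.

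- **Options.** The abstract (Methods) lists three arms: "Patient participants will be randomised to one of three groups: fixed-period six month recall, risk-based recall, or fixed-period twenty-four month recall". Under Recall strategy allocation, the 24-month arm exists only in stratum 1, where it competes with the other two. Stratum 2 has risk-based and six-month recall only.
- **Economic question.** Estimation of cost-effectiveness asks whether 24-month or risk-based recall is an efficient use of NHS resources "compared to the traditional fixed-period six-month recall".
- **Cost per QALY.** The ratio is obtained by "dividing the difference in mean total costs by the difference in QALYs between the arms of the Trial", and "This ratio can be compared to the conventional threshold of £30,000 per QALY".
- **Uncertainty in the QALY analysis.** Bootstrapping produces the CEAC, which is defined in one sentence: "The CEAC shows the probability that the different recall strategies are cost-effective compared to usual care at various thresholds of cost-effectiveness".
- **Cost-benefit analysis.** Net benefits based on willingness to pay have a selection rule: "The recall strategy with the highest incremental net benefit compared to six-monthly recall is the most efficient option". A net benefit curve then gives the chance that net benefits exceed a range of thresholds.
- **Promise.** Objectives states: "The cost-effectiveness and cost-benefit of the three recall strategies will also be assessed as part of the economic evaluation". The abstract (Discussion) says that "INTERVAL will provide evidence for the most clinically-effective and cost-beneficial recall interval".

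**The concern.** A curve against one shared comparator answers whether a strategy beats six-month recall. With three mutually exclusive options, the decision question is which of the three has the highest net benefit, and how sure we are of that. Both pairwise curves use the same six-month arm, so their values are positively correlated, need not sum to one, and contain no comparison of 24-month with risk-based recall.

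For patients judged suitable for 24-month recall, that missing comparison is a real commissioning choice. A reader who sees two high curves could take each as strong support for its strategy, although both cannot be the best.

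**Working it through.** The plan states no figure here to reproduce: it gives no cost or QALY means or variances. The mechanism can be shown in general, and its size only under assumptions.

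**1. Definitions.** At one threshold, let N6, N24 and NR be the mean net monetary benefits of six-month, 24-month and risk-based recall.
- The plan's CEAC value for strategy k is P(Nk > N6).
- The probability of being best is P(Nk is the largest of the three).

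**2. Direction, with no inputs.** Being the largest of three requires beating six-month recall and also the other alternative. So the probability of being best can never exceed the pairwise value. The three probabilities of being best sum to one. The two pairwise values are under no such constraint.

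**3. Point ranking.** (N24 − N6) − (NR − N6) = N24 − NR. Subtracting the same reference leaves the order of the alternatives unchanged, so the selection rule in the cost-benefit analysis names the correct leader on point estimates. What is missing is the probability attached to that choice.

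**4. Illustration with chosen pairwise values.** Assume independent arm means, each normal with standard error 1. Then P(Nk > N6) = Φ(μk/√2), so μk = √2 × Φ⁻¹(pairwise value).
- 90% and 90%: μ = 1.2816 × 1.4142 = 1.812 for both.
- 95% and 85%: μ = 1.6449 × 1.4142 = 2.326, and 1.0364 × 1.4142 = 1.466.

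P(k is best) = ∫ φ(x − μk) ∏ Φ(x − μj) dx over the other two arms j. The results were checked by simulation and by numerical integration.

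| Pairwise, A / B | Best: A | Best: B | Best: six-month |
|---|---|---|---|
| 90% / 90% | 48% | 48% | 3% |
| 95% / 85% | 71% | 26% | 2.5% |

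**5. Illustration at the planned stratum 1 size.** The Sample size section gives 235 per arm. The advantages over six-month recall and the standard deviations (SD) of net monetary benefit are assumptions. The standard error per arm is SD/√235, for example 3,000/15.33 = £196.

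| Assumed advantage, A / B | Assumed SD | Pairwise, A / B | Best: A / B / six-month |
|---|---|---|---|
| £500 / £500 | £1,500 | 1.00 / 1.00 | 0.50 / 0.50 / 0.00 |
| £500 / £500 | £3,000 | 0.965 / 0.965 | 0.50 / 0.50 / 0.01 |
| £500 / £500 | £6,000 | 0.82 / 0.82 | 0.46 / 0.46 / 0.08 |
| £500 / £600 | £3,000 | 0.965 / 0.985 | 0.36 / 0.64 / 0.00 |

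In the last row the two pairwise values are almost the same, while the probabilities of being best are 36% and 64%.

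**6. Scope.** The Sample size section plans 705 participants in stratum 1 and 1030 in stratum 2. So 1030/1735 = 59% of participants are in a stratum with two options, where a pairwise curve is complete. The point concerns the 705.

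**The case against.** The strongest case on the other side has four parts.

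- **The plan can choose a winner.** A reader might infer from the pairwise curves that the trial cannot say which interval is best. The article does not support that. It has an explicit rule (highest incremental net benefit against six-monthly recall), step 3 shows that this rule ranks correctly, and the cost-per-QALY ratio is taken between trial arms without restriction to comparisons with six-month recall. The promise of the most cost-beneficial interval fits most closely with the cost-benefit analysis, which contains the rule. This part stands in full.
- **The article is condensed.** A fuller economic plan may specify a joint curve, and what an article leaves to it is not missing. This stands for the incremental analysis, which the article neither sets out nor excludes. It stands less well for the CEAC, because the article does not leave the curve open: it gives a definition, and that definition is pairwise.
- **The pairwise curve answers the question as framed.** The stated question is against six-month recall, and in the illustrations of step 4 six-month recall is best in only about 3% of draws. This is true, so the curve is not wrong about its own comparison. It does not cover the assessment of all three strategies set out in Objectives.
- **The numbers are chosen.** It is tempting to read the gap between 90% and 48% as the size of an error. It is not: the two figures are different probabilities, the inputs are assumed, and the even split follows from assuming tied alternatives.

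The label usual care is an editorial matter, since the same section names six-month recall as the comparator.

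**Conclusion.** The point holds as a weakness in how decision uncertainty is defined, limited to stratum 1. The plan will name a best strategy on point estimates. It does not describe any quantity that says how likely that strategy is to be the best of the three: the CEAC compares with six-month recall, and the net benefit curve gives the chance of exceeding thresholds.

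The direction is certain, because the probability of being best cannot exceed the pairwise value. The size is not known from the article. With equal standard errors and independent arms, two pairwise values of 90% correspond to about 48% each. With 235 per arm, tied £500 advantages and SDs of £1,500 to £6,000, pairwise values of 0.82 to 1.00 correspond to 0.46 to 0.50. The gap for the leading strategy narrows as the two alternatives separate.

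This affects the economic evaluation only, and it can be corrected before analysis. It is worth changing because the stated definition leaves out the uncertainty that decision-makers need when three options compete.

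**What to change.** In Estimation of cost-effectiveness:

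1. For stratum 1, define the CEAC at each threshold as the share of bootstrap replicates in which each of the three strategies has the highest net monetary benefit. Compute all three on the same replicates, so that the curves sum to one.
2. For stratum 1, report the full incremental analysis with the strategies ordered by cost, including 24-month versus risk-based recall.
3. Keep the two-strategy curve for stratum 2 and for the pooled six-month versus risk-based contrast.
4. Name six-month recall as the reference in place of usual care.

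The cost is a reworded definition and a few lines of extra analysis on bootstrap replicates already planned, with no new data or participants. The price in presentation is that the stratum 1 curves may look less decisive than the pairwise ones.

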### Missing data

Two approaches will be used to deal with any missing data. The data will first be analysed using complete cases only. This may lead to biased and incorrect results if a relatively large proportion is missing. Multiple imputation using iterative chained equations is therefore also used to impute missing values. Data are imputed at each time point based on an iterative algorithm, imputing five datasets, adjusting for baseline characteristics. Data will be predicatively mean matched to fit within the range of the available data.

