### Sensitivity analysis

Univariate sensitivity analysis is used to examine the impact of the discount rate, uncertainty surrounding the unit cost data, missing data, centre-specific variation.

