### Likely rate of loss to follow-up

In the power calculation we have assumed a loss to follow-up for dentists of 10% based on the observed rates of 12 and 9% in two recent large, multi-centre practice based RCTs [19]. For patient participants it is anticipated that loss to follow-up will be not more than 15% at 4 years. This estimate is based on a practice based trial conducted in North-West England where 79% of 4211 participants were retained for a period of 5 years [20]. In a recent trial conducted in a similar population 78% of participants returned a follow-up postal questionnaire. In this trial we anticipate a lower loss to follow-up because we will be using a more intensive reminder system and will explore the use of evidence based strategies to improve response.

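### Multiple imputation is fixed at five datasets, too few for reproducible results at the losses the protocol itself plans for

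*Protocol article*

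**What the plan says.** The Missing data section sets out two approaches. First, "The data will first be analysed using complete cases only". The section warns that this can bias results when much is missing, and continues: "Multiple imputation using iterative chained equations is therefore also used to impute missing values". The specification is then "Data are imputed at each time point based on an iterative algorithm, imputing five datasets, adjusting for baseline characteristics", and "Data will be predicatively mean matched to fit within the range of the available data".

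The section follows the economic analysis sections. The paragraph after it is also economic: "Univariate sensitivity analysis is used to examine the impact of the discount rate, uncertainty surrounding the unit cost data, missing data, centre-specific variation". Its opening sentence nevertheless speaks of missing data without restriction.

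Under Likely rate of loss to follow-up, the power calculation assumes 10% loss of dentists, and for patients "it is anticipated that loss to follow-up will be not more than 15% at 4 years". The two losses are not combined anywhere. The same section mentions a similar trial with 78% return of a follow-up postal questionnaire and expects to do better. Under Estimation of benefits, QALYs are the area under EQ-5D-3L utilities measured at baseline and annually.

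**The concern.** Multiple imputation adds simulation error that depends on the random seed and shrinks only as the number of datasets grows. Five is a published figure, so it is a stated choice and not a detail left open. With 15 to 25% of the information missing, five datasets leave an error large enough that two analysts running the same plan on the same data, with different seeds, could report visibly different incremental costs, QALYs, intervals and acceptability curves. The interval width is also affected, because the between-imputation variance is estimated from five values, that is, on four degrees of freedom. The cost-utility result is to be read against a £30,000 per QALY threshold (Estimation of cost-effectiveness), so noise of this kind matters most when the strategies are close.

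**Working it through.** **The plan's own figures.** The protocol gives neither a combined missing fraction nor a simulation error, so on this point there is nothing to reproduce. The sample-size figure used below to scale a simulation does reproduce: 2 × (1.960 + 1.282)² × 25² / 7.5² = 233.5, so 234 per arm against the stated 235.

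**Missing fraction.**
- Patient loss alone: 15%.
- Patient and dentist loss, if every patient of a lost dentist is missing: 1 − 0.90 × 0.85 = 23.5%.
- Cross-check from the recruitment target: 705 + 1030 = 1735 and 1 − 1735/2372 = 26.9%. Since 1735/0.765 = 2268, the target of 2372 is not exactly these two losses applied to 1735. I use 26.9% only as an outer value.
- QALYs: no figure is given. If 78% return held independently at each of four annual follow-ups, 0.78⁴ = 37% would have all four. That is an outer case, because the trial expects better return, non-response tends to recur in the same people, and partial records still carry information. I assume 40 to 50% missing information as an illustrative range.

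**Formulas**, with f the fraction of missing information (taken as equal to the missing fraction) and m the number of datasets:
- seed-to-seed SD of the pooled estimate, in standard errors = √(f/m)
- relative efficiency = 1/(1 + f/m)

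| f | SD, m = 5 | Efficiency, m = 5 | SD, m = 25 | SD, m = 50 |
|---|---|---|---|---|
| 15% | 0.173 | 0.971 | 0.077 | 0.055 |
| 23.5% | 0.217 | 0.955 | 0.097 | 0.069 |
| 40% | 0.283 | 0.926 | 0.126 | 0.089 |
| 50% | 0.316 | 0.909 | 0.141 | 0.100 |

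**Check by simulation.** Predictive mean matching with m = 5; SD 25; effects of 7.5 points (235 per arm after losses) and 4.5 points (750 per arm after losses); 23.5% or 27% missing completely at random; assumed correlation of 0.4 between a baseline covariate and the outcome. Repeating the imputation with new seeds on the same data gave a seed SD of 0.21 to 0.23 standard errors, in agreement with the formula.

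**What this means for an acceptability curve.** Suppose incremental net benefit is normal and the true probability of being cost-effective is 50%. One seed SD moves that probability to Φ(0.173) = 57% or Φ(0.217) = 59% at m = 5, and to Φ(0.316) = 62% at 50% missing information. At m = 50 the corresponding values are Φ(0.055) = 52%, Φ(0.069) = 53% and Φ(0.100) = 54%.

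**Treatment arm in the imputation model (conditional).** In the same simulation, with arm in the model, 97 to 100% of the true difference was recovered. With arm left out, 73 to 76% was recovered, which is close to one minus the missing fraction.

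**The case against.** The strongest reply is that five imputations are weak but not wrong. Efficiency is about 95% at 23.5% missing, and the pooling rule carries the simulation error into the interval through its (1 + 1/m) term. That stands, and it is why the point concerns reproducibility and not validity.

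The 23.5% can also be challenged. Questionnaires go by post, clinical outcomes are taken by trained outcome assessors, and NHS treatment costs come from routine databases, so patients of a lost dentist need not be missing. This stands too, but at 15% the seed SD is still 0.17 standard errors. Repeated annual scores may lower the missing information further; for QALYs, missed waves push the other way.

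Fifty is partly a matter of preference. At 23.5% missing, 25 datasets already give 0.10 standard errors and 0.99 efficiency. With QALYs more exposed and computing cheap, about 50 is a reasonable round figure.

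Three stronger readings are tempting, and the document does not support them:
- A reader might infer that only baseline variables enter the imputation and that arm differences are therefore diluted. The text says the imputation adjusts for baseline characteristics; it does not say that nothing else is used. Chained equations ordinarily use the other incomplete variables too. Arm is neither included nor excluded, and a predictor list is detail that a condensed article may leave to the analysis plan.
- A reader might infer that the primary bleeding and OHIP-14 comparisons could cross a significance threshold by choice of seed. The section sits among the economic analyses, and imputing at each time point does not fit bleeding, which is assessed at four years. Application to the primary outcomes is possible but not established.
- A reader might infer that complete-case and imputed results have no order of precedence. Complete cases come first and missing data is listed under Sensitivity analysis, so a base case followed by a sensitivity analysis is a natural reading. Explicit labelling can be left to the analysis plan.

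**Conclusion.** The point holds for the number of imputations. Five datasets leave a seed-to-seed SD of about 0.17 to 0.22 standard errors at the plan's own losses, and about 0.28 to 0.32 for QALYs at an assumed 40 to 50% missing information. This rests on equating missing information with the missing fraction and, for the upper planning figure, on adding the dentist loss in full. The consequence is avoidable instability in the imputed estimates, intervals and acceptability curve, most clearly for costs and QALYs. No bias and no invalid inference is shown. Whether arm and stratum are in the imputation model is a question to put to the authors, not a demonstrated error.

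**What to change.** In the Missing data section, or in the analysis plan with a note that it supersedes the article, replace five datasets with about 50. The seed SD then falls to 0.05 to 0.07 standard errors at 15 to 23.5% missing, and to at most 0.10 at 50%. The cost is a change of one number and ten times as many imputed datasets to process, a matter of minutes of computing. Data collection and sample size are unaffected.

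As a clarification, add one sentence confirming that arm and randomisation stratum are in the imputation model, or that imputation is done separately by arm. If arm were left out, the arm difference would shrink roughly in proportion to the missing fraction.
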